### Blood sample collections

Blood is drawn from the cubital vein between 8:00 and 9:00 AM, in fasting state. A total of thirty millilitres of blood was drawn from each individual at baseline and at each phase of FU. The blood is divided as shown in Fig. 2. Plasma cortisol, ACTH, vitamin B12, folic acid, albumin and creatinine have been assessed.

**Fig. 2 Fig2:**
[figure not shown]
Schematic of blood processing. Composition of buffer B: 10 mM Tris-HCl pH 7.4, 10 mM EDTA, 0.1 mM PMSF, 0.01 mg/l aprotinin and 0.01 mg/l leupeptin. Density of Ficoll-Hypaque = 1.077 g/ml. Storage temperature of isolated samples = −80 °C. *PRP* platelet-rich plasma, *PBMC* peripheral blood mononuclear cell, *RT* room temperature

### tPLA_2_ activity determination

tPLA_2_ enzymatic activity is determined by a commercial kit (cPLA_2_ Assay Kit, Cayman Chemical Company, Michigan, USA), normalized by protein concentration and expressed as nmol/min/mg. Since samples are not preliminarily purified for sPLA_2_ or treated by iPLA_2_-specific inhibitors, the data obtained can be referred to tPLA_2_. All samples are measured in duplicate. Protein concentration is determined by the Lowry method [39].

### mRNA BDNF determination (qRT-PCR)

Peripheral blood mononuclear cells (PBMCs) are isolated by conventional density gradient centrifugation, and the lymphocytes are separated from the monocytes using Dynabeads Untouched Human Monocytes kit (Invitrogen, USA). This determination method is shown in Casoli et al. [19].

### Plasma BDNF assay

Plasma levels of BDNF are measured using commercial enzyme-linked immunosorbent assay (ELISA) method (BDNF Human ELISA kit, ABCAM, Cambridge, UK), according to the manufacturer’s instructions. All samples and standards are measured in duplicate, and the means of the duplicate are used for statistical analyses. The detection limit for BDNF is typically less than 80 pg/ml.

### Ratio between platelet APP forms

The samples were separated on 7.5 % SDS–PAGE and electrotransferred to nitrocellulose membranes. After blocking with 5 % non-fat dry milk, the membranes were incubated with monoclonal 22C11, diluted 1:1000 (Becton–Dickinson). Blots were visualized using the enhanced chemiluminescence detection kit (Amersham Biosciences). The results are expressed as the ratio between the optical density of the upper (130-kDa) and the lower (106- to 110-kDa) APP immunoreactive bands using β-actin as the internal standard.

### Oxidative stress level

For the determination of oxidative stress, the d-ROMs test (Diacron, Grosseto, Italy) has been used. It is based on Fenton’s reaction, and the values will be expressed as equivalent units (0.08 mg/dl) evaluated by means of free radicals and antioxidant systems (FRAS, Diacron, Grosseto, Italy).

### Trace elements determinations in human plasma

Plasma zinc (Zn), copper (Cu), iron (Fe) and selenium (Se) levels are determined by a Thermo XII Series ICP-MS device (Thermo Electron Corporation, Waltham, MA, USA) following the method previously reported [40].

### Monocyte isolation, RNA extraction, expression profiling and data analysis

Total RNA was extracted from the monocytes using the RNeasy Mini Kit (Qiagen, Hilden, Germany) as recommended by the manufacturer. Purified RNA was quantified using a NanoDrop spectrophotometer, and RNA integrity was determined by gel electrophoresis. The microarray procedure was performed according to the Affymetrix protocols (Santa Clara, CA, USA). Hybridization cocktails containing fragmented, end-labelled single-stranded cDNA were prepared and hybridized to GeneChip Human Exon 1.0 ST arrays (Affymetrix, Santa Clara, CA, USA). Washing and scanning were performed using GeneChip^®^ Fluidics Station 450 and GeneChip^®^ Scanner 3000 7G (Affymetrix Inc.) and converted to numerical data using GeneChip^®^ Command Console^®^ Software (AGCC). The microarray data analysis will be performed by Partek Genomics Solution 6.6 software (http://www.partek.com). The robust multi-array analysis (RMA) of Irizarry et al.’s algorithm will be used for probe set (exon-level) intensity analysis. Exon-level data will then be filtered to include only those probe sets that are in the “core” meta-probe list, which represents 17 800 RefSeq genes and full-length GenBank mRNAs. Within this gene set, the analysis of variance (ANOVA) and multi-test correction for *P* values in Partek Genomic Suite will be used to identify alternative splicing events. A list of genes with significant alternative spliced events will be generated by using a 0.05 FDR criterion as a significant cut-off. The genes will be sorted based on gene function using Partek Pathway software.

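### The splicing pipeline filters exon-level data by annotation only, so a whole-gene expression shift can be listed as splicing where some probe sets are silent in monocytes; the 0.05 FDR does not prevent it

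*Protocol article*

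**What the plan says.** The section of the Protocol article on monocyte isolation, RNA extraction, expression profiling and data analysis gives the pipeline in order.

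- **Source.** One cell type: "Total RNA was extracted from the monocytes using the RNeasy Mini Kit".
- **Summarisation.** RMA, whose "algorithm will be used for probe set (exon-level) intensity analysis".
- **Filter.** One criterion is named, membership of the core annotation list: "Exon-level data will then be filtered to include only those probe sets that are in" that list. Its stated coverage is 17 800 annotated genes and mRNAs.
- **Test.** Within that gene set, ANOVA with multiple-test correction "will be used to identify alternative splicing events". The model terms and the groups compared are not given.
- **Output.** "A list of genes with significant alternative spliced events will be generated by using a 0.05 FDR criterion as a significant cut-off". The listed genes are then sorted by function.

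No criterion for signal above background is stated, for probe sets or for genes. The array analysis is written in the future tense.

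**The concern.** Membership of the core list is a matter of annotation. It shows that a probe set belongs to a well-documented transcript, not that it gives signal in monocytes.

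A splicing ANOVA of the usual kind asks whether the group difference varies across the probe sets of a gene. A probe set at background stays flat when the whole gene goes up or down. The difference then does vary across probe sets, and the gene is called spliced although its splicing is unchanged.

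FDR control limits chance rejections of true nulls. Here the statistical null is false for a non-biological reason, so the correction leaves the call in place and more arrays make it more certain.

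The splicing list is the only array result this section plans, and it feeds the functional sorting. Monocyte profiling is among the biomarkers named in the Introduction, and identifying markers correlated with training is a secondary outcome. An ordinary expression change could be reported there as a splicing change.

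**Working it through.** The plan has no figure to reproduce here: 0.05 is a chosen threshold. Two checks show whether the mechanism works and what its size depends on.

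**Inputs from the article:** 17 800 genes, annotation filter, ANOVA, FDR 0.05. **Everything else is assumed**, including that the ANOVA tests the probe-set by group interaction.

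**Check 1: one affected gene (noncentral F).** Assume J = 10 probe sets, k of them silent, no splicing change, n arrays per group and residual SD σ of 0.25 to 0.40 log2. The shift is D = log2(fold change) in the responding probe sets and 0 in the silent ones.

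- λ = (n/2) × Σ(δj − mean δ)² / σ², where Σ(δj − mean δ)² = D² × k(J − k)/J
- df1 = J − 1 = 9; df2 = (J − 1)(2n − 2), which is 882 for n = 50 and 342 for n = 20
- Cut-off P < 0.001, a stand-in for the FDR rule. Benjamini-Hochberg at 0.05 over 17 800 genes has this cut-off when 0.001 × 17 800 / 0.05 = 356 genes are listed.

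Example: 1.2-fold, k = 2, n = 50. D = 0.263, and the sum is 0.0692 × 1.6 = 0.1107. With σ = 0.40, λ = 25 × 0.1107 / 0.16 = 17.3 and the probability of a call is 0.38. With σ = 0.25, λ = 25 × 0.1107 / 0.0625 = 44.3 and the probability is 0.98.

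Probability that the unspliced gene is called (σ = 0.40 to σ = 0.25):

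| Arrays per group | Silent | 1.2-fold | 1.3-fold | 1.5-fold |
|---|---|---|---|---|
| 50 | 2 of 10 | 0.38–0.98 | 0.92–1.00 | 1.00 |
| 50 | 1 of 10 | 0.11–0.68 | 0.50–0.99 | 0.99–1.00 |
| 20 | 2 of 10 | 0.05–0.38 | 0.25–0.92 | 0.88–1.00 |
| 20 | 1 of 10 | 0.02–0.11 | 0.07–0.50 | 0.44–0.99 |

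At P < 0.0001 the 50-array, two-silent, 1.2-fold entry falls to 0.19–0.92. With k = 0, λ = 0 whatever the shift, and the gene is called only at the nominal rate.

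**Check 2: a whole list (simulation, one run per setting).** 17 800 genes, 10 probe sets each, residual and array SD 0.3 log2, 2% of genes truly spliced, 10% shifted as a whole, 3 of 10 probe sets silent in 40% of genes, Benjamini-Hochberg at 0.05. Realised false discovery proportion:

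| Setting | 10 per group | 25 | 50 |
|---|---|---|---|
| No shift, none silent | 0.06 | 0.05 | 0.04 |
| Shift 0.5 log2, none silent | 0.03 | 0.05 | 0.04 |
| No shift, silent present | 0.08 | 0.14 | 0.12 |
| Shift 0.2, silent present | 0.21 | 0.31 | 0.52 |
| Shift 0.5, silent present | 0.57 | 0.68 | 0.69 |
| Shift 1.0, silent present | 0.67 | 0.71 | 0.71 |

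With the silent probe sets removed before the ANOVA, all nine shifted settings return to about 0.04–0.06. The simulation knows which probe sets are silent; a real detection rule would do somewhat less well.

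The top of the range follows from the assumed frequencies. Shifted, unspliced genes with silent probe sets number 17 800 × 0.10 × 0.40 × 0.98 = 698, against 17 800 × 0.02 = 356 truly spliced. If all were called, 698/(698 + 356) = 0.66 of the list would be artefact before any other false call. Were 2% of genes shifted instead of 10%, the same sum gives 140/(140 + 356) = 0.28.

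**The case against.** **Article format.** A detection filter is preprocessing detail that a condensed article may leave to the full protocol, and it could coexist with the annotation filter. The silence does not prove that no such filter exists. It still carries weight: the article describes its filtering step, names one criterion and says the ANOVA runs within the resulting set. Followed as written, silent probe sets enter the test.

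**Unstated model.** The mechanism assumes an interaction test, and the article says only ANOVA. This stands as a limit on the argument. It does not rescue the plan: if single probe sets were compared between groups, plain shifts would be listed with or without a detection filter. The model therefore needs stating too.

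**Stronger readings.** A reader might infer that expression shifts in general will be listed as splicing. The article does not support that, and the second row of the simulation table shows no excess when every probe set is expressed. A reader might also infer that most of the list would be wrong. The table in check 1 is conditional on a gene already being affected, and the simulated proportions rest on invented frequencies. Saturated probe sets or differences in cell purity could be imagined as further routes, but the article gives nothing on either, and they are not relied on here.

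**Reach.** The primary outcome, sample size and randomisation are untouched. That is right and limits the weight of the point.

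**Conclusion.** The point holds in conditional form. The only stated filter is by annotation, and the stated error control cannot remove calls caused by silent probe sets in a shifted gene. Both conditions must be present in the same gene, and the splicing test must be the probe-set by group interaction.

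The size cannot be fixed from the article. It depends on array numbers, variances, probe sets per gene, the share of silent probe sets and the frequency of whole-gene shifts, none of which is given. The calculations show that the effect can range from negligible to dominant, and that removing silent probe sets largely cures it. It is worth correcting before the array data are analysed, as a matter for a secondary biomarker result of exploratory character.

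**What to change.** In the array data-analysis section, after the core filter and before the ANOVA:

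1. Exclude probe sets that are detected above background in neither of the compared groups, with the detection rule fixed in advance.
2. Test a gene for splicing only if it is expressed in both groups.
3. State that splicing is judged by the probe-set by group interaction.
4. Show the gene-level fold change beside each splicing call.
5. Keep and flag probe sets detected in only one group, as possible exon switching.

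Do not require that a call persist after non-responding probe sets are removed. An exon that fails to follow its gene is also what true differential splicing looks like, so that rule could delete real events.

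The cost is a filtering step and some reporting, with no new assay. The downside is a shorter gene list.

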## Introduction

Cognitive decline and dementia are pathological conditions that may heavily affect social functioning and independent living. Elderly are particularly susceptible to cognitive diseases, particularly mild cognitive impairment (MCI). Previous studies have evidenced that the annual conversion rates from MCI to Alzheimer’s disease (AD) vary from 5 to 20 % [1], with higher rates in subjects with subjective memory complaints.

To reduce the incidence of these diseases, it is pivotal to identify the treatments that prevent or delay the cognitive decline as well as its progression to dementia. Pharmacological therapies currently available have been proved to be no effective [2], but positive results have been shown by the use of cognitive training, in particular to enhance or regain specific functions, such as memory and attention processes, with a positive impact on subjective well-being, mood status and quality of life of elderly people [3].

The identification of the processes involved in cognitive decline is another key issue, and a multidisciplinary approach might be particularly suitable.

The “My Mind Project” aimed to analyse several aspects related to cognitive performances before and after a cognitive and comprehensive intervention as well as the possible changes in potentially related peripheral biomarkers. Indeed, the variations in cognitive status can be reflected by the modulation of systemic biological parameters. We decided to focalize the attention on the following biomarkers: brain-derived neurotrophic factor (BDNF, lymphocytes mRNA and plasmatic protein), platelet total phospholipase A_2_ (tPLA_2_) activity, the ratio between the levels of two platelet amyloid precursor protein (APP) forms, trace elements, monocyte expression profiling as well as oxidative stress evaluation.

BDNF, a neurotrophin associated with activity-dependent synaptic modulation, is widely expressed in brain structures involved in learning and memory and is also produced by immunocompetent cells [4]. Many studies have taken into account the peripheral blood BDNF levels in AD patients, but data are controversial. Discrepancies are difficult to explain as they might be due to heterogeneity in disease staging [5], not the evaluation of drug use and depressive symptoms [6], underestimation of smoking and alcohol intake impact [7].

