PLA_2_ comprises a superfamily of enzymes involved in a wide variety of physiological processes, including phospholipid metabolism, remodelling of cell membranes and intracellular signalling. Cerebral PLA_2_ influences the non-amyloidogenic processing of APP [8], and its functional alterations may have consequences on amyloid-beta peptides (Aβ) production. The use of platelet tPLA_2_ as peripheral biomarker of the neuronal enzyme is peculiarly convincing in the light of the recent finding that *total* PLA_2_ activity in the thrombocytes may specifically mirror the *total* activity in the brain [9].

Aβ, present in the extracellular plaques of AD brain tissue [10], originates by proteolytic processing of APP, a transmembrane protein abundantly expressed in the brain and the peripheral tissues such as platelets. It has been reported that AD platelets show a reduced ratio between the levels of two APP forms, observed as two immunoreactive bands at 130 and 106–110 kDa in Western blotting assays. The APP form ratio allows to detect AD at an early stage and to differentiate it from other types of dementia [11].

Another important aspect regards the role of the immune system in AD pathogenesis. Several evidences support the idea of a brain–immune system breakdown as a potential pathological mechanism in AD [12]. In AD, mononuclear phagocytes (MP) are inefficient [13], and the accumulation of the metabolic end-product Aβ might be due to the failure of the innate immune system. The molecular mechanisms and the gene pathways involved in monocytes deregulation are unknown. Taking into account that also trace elements are essential for optimal immune system function [14], it is increasingly important to understand the process that governs this response in AD. In recent years, it has become evident that trace elements, particularly zinc (Zn), copper (Cu), iron (Fe) and selenium (Se), may play a role in the pathogenesis of AD [15]. Conversely, the possible relationship existing among plasma trace elements levels and performance on cognitive function tests is not well known.

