### Secondary outcomes

They includeThe assessment of the effects of intervention and the relationship between psychological status, lifestyle characteristics, functional and health status, biochemical aspects by the use of a multidisciplinary approach.The investigation of rate of percentage of subjects with MCI who converted to dementia.The identification of biochemical markers correlated with the cognitive training in HE, MCI, AD.

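### The array analysis described tests only for alternative splicing, although the announced biomarker is monocyte expression profiling; even changes in a gene's overall expression would be missed

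*Protocol article*

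**What the plan says.** Three places in the protocol article bear on this.

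- **What is announced.** The Introduction lists the chosen biomarkers, ending with "monocyte expression profiling as well as oxidative stress evaluation". The methods section on the arrays is headed "Monocyte isolation, RNA extraction, expression profiling and data analysis".
- **What it is for.** Under Secondary outcomes, the item that covers the biomarkers is "The identification of biochemical markers correlated with the cognitive training in HE, MCI, AD". As background, the Introduction also remarks: "The molecular mechanisms and the gene pathways involved in monocytes deregulation are unknown".
- **What will be done.** In the array section, the RMA "algorithm will be used for probe set (exon-level) intensity analysis". The data are then filtered to the core probe sets, "which represents 17 800 RefSeq genes and full-length GenBank mRNAs". ANOVA with correction for multiple testing "will be used to identify alternative splicing events". The output is stated: "A list of genes with significant alternative spliced events will be generated by using a 0.05 FDR criterion as a significant cut-off". A last sentence has the genes sorted by function in pathway software, which in sequence means the genes on that list.

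The Statistical analysis section gives a repeated-measures ANOVA for biochemical parameters and does not mention expression data.

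**The concern.** Expression profiling ordinarily means asking which genes are up- or down-regulated. A splicing test asks whether particular exons behave differently from the rest of their gene between conditions. A gene whose exons all move together gives no splicing signal, so it reaches neither the list nor the function step.

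At stake is part of the secondary aim of finding markers correlated with training. The arrays would contain the information on overall expression, but the analysis described does not extract it. A short or empty list would say little about expression, and a gene-level list added after the results are known would look data-driven. The article puts the array data analysis in the future tense, so the point could still be settled in advance when it was written.

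**Working it through.** The plan gives no figure to reproduce. The check has two parts: what the splicing test can see, and how much that matters in an illustrative setting.

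**1. Structure of the test.** Write the log2 intensity of exon *e* in subject *i* (group *g* = 0 or 1) as

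y(i,e) = m(e) + d·g + b(e)·g + s(i) + r(i,e), with the b(e) averaging zero over exons,

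where *d* is an even shift of the whole gene, b(e) the exon-specific departure, s(i) the subject effect and r(i,e) the residual. The splicing question is whether all b(e) = 0. The group-by-exon interaction uses each exon's deviation from the subject's own gene mean:

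y(i,e) − ȳ(i) = [m(e) − m̄] + b(e)·g + [r(i,e) − r̄(i)].

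The shift *d* cancels. If the gene changes evenly, the interaction test rejects at its alpha, whatever the size of *d* or the number of subjects. A gene-level test on ȳ(i) estimates *d* directly.

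**2. Illustration.** The documents give none of these inputs, nor the number of subjects arrayed. All are assumptions: 25 arrays per group, 10 core probe sets per gene, between-subject SD 0.4 and residual SD 0.3 (log2 scale), two-sided P < 0.001 as a stand-in for a genome-wide threshold.

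- SD of a subject's gene mean: √(0.4² + 0.3²/10) = √0.169 = 0.411
- Standard error of the group difference: 0.411 × √(2/25) = 0.1163
- Critical t, 48 df, two-sided 0.001: 3.505

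| Even shift (log2) | Noncentrality | Gene-level t test | Splicing test |
|---|---|---|---|
| 0.50 | 0.50/0.1163 = 4.30 | 78% | 0.1% (= alpha) |
| 0.75 | 0.75/0.1163 = 6.45 | over 99% | 0.1% (= alpha) |

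The gene-level figures come from the noncentral t distribution. A simulation of 4,000 runs gave 79% and over 99%, with 0.08% and 0.05% for the splicing test, as expected up to simulation error.

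**3. Dependence on the assumptions.** With the shift held at 0.5 log2 and 10 probe sets, the gene-level power at P < 0.001 is:

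| Arrays per group | Subject SD 0.3 | Subject SD 0.4 | Subject SD 0.6 |
|---|---|---|---|
| 10 | 40% | 17% | 4% |
| 25 | 98% | 78% | 29% |
| 50 | over 99% | over 99% | 76% |

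The splicing test stays at 0.1% in every cell.

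**4. The reverse case.** In a separate simulation (2,000 runs per setting, 10 or 50 subjects per group, 5 or 10 exons, both SDs 0.3, alpha 0.05), the splicing test rejected in 4% to 6% of runs under an even shift of 0.3 or 0.6, and the gene-level test in 49% to 100%. With a shift of 0.6 in one exon only, the splicing test rejected in 85% to 100% and the gene-level test in 7% to 45%. The two tests answer different questions, and neither replaces the other.

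**The case against.** **Splicing is a coherent choice.** Exon arrays, exon-level normalisation, an ANOVA for splicing events and an FDR-controlled list fit together, and splice-variant profiling can loosely be called expression profiling. This stands as far as it goes: the splicing analysis is not wrong in itself. The difficulty is that the announced label is broader than the analysis.

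**A condensed article may leave a gene-level analysis to the full protocol.** This is possible. A reader might infer that gene-level analysis has been ruled out, and the article does not say so. But the section does not leave the array analysis open. It fixes the software, normalisation, probe filter, test, purpose, FDR threshold and output, and the inferential steps all concern splicing. The point is therefore a mismatch between a stated method and a stated biomarker, and not only missing detail.

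**There is no pathway endpoint.** A reader might go further and conclude that the plan poses a pathway question it cannot answer. The documents do not support that. The sentence about unknown gene pathways is background, the secondary outcomes name no pathway or gene-level endpoint, and a function-sorting step is planned. A splicing list can inform on pathways through splice variation, so the answer is restricted and not impossible.

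**The simulation shows what the algebra already shows.** Correct. The near-null figure for the splicing test is its alpha by construction, the gene-level figure depends on assumed inputs, and P < 0.001 is not the plan's FDR criterion. The numbers illustrate a property of the tests; they do not measure a loss in this trial.

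**Harm is speculative.** Largely fair. The output is labelled as a splicing list, and nothing shows that the investigators would read an empty list as absence of any deregulation.

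**Conclusion.** The point holds in a limited form. The array analysis described covers alternative splicing only, and the function step follows from that list, while the article announces expression profiling and seeks markers correlated with training. Genes that change evenly across their exons would be picked up only at about the false-positive rate. That result follows from the structure of a splicing test and needs no assumed values. How many such genes a gene-level test would find does depend on assumptions: about 78% in the base illustration, and from 4% to over 99% across the settings shown.

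This concerns one exploratory biomarker among several. The primary outcome, sample size and efficacy analysis are untouched, and the array data are not lost. It is a cheap improvement of minor weight.

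**What to change.** Either of two changes reconciles the passages.

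1. **If overall expression is of interest:** summarise the core probe sets to one value per gene. Test the change in the experimental v the control group within each of HE, MCI and AD, and the differences across these three groups, at FDR 0.05. Take that list to the function and pathway step. Keep the splicing ANOVA as a separate analysis with its own FDR-controlled list. Write this down before the array results are seen.
2. **If only splicing is intended:** restate the biomarker in the Introduction and in the heading of the array section as splice-variant profiling, and limit the conclusions to that.

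The first option needs no further samples or arrays, only some extra analysis of the same data; its downside is a second FDR-controlled list to report. The second costs a change of wording and gives up any conclusion on overall expression.
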